#### Secondary endpoints for the different surveillance measures

- Comparison of initial rate of consent between the groups [Modules 1-4]
- Comparison of rate of acceptance between the groups [Modules 1-3]

#### Secondary endpoints regarding acceptance by parent/child groups

- Drop out rate of parents (withdrawal of initial consent), reasons for withdrawal of consent
- Drop out rate of children (proportion of scheduled samples refused), overall and stratified by age groups
- Drop out rate over time (weekly, cumulative)

#### Secondary endpoints regarding acceptance by childcare workers

- Initial rate of consent of childcare workers (proportion of childcare workers with signed informed consent forms among all childcare workers contacted)

#### Secondary endpoints regarding acceptance by daycare centers

- Initial rate of consent of contacted daycare centers to study participation (proportion of centers consenting to participation among all daycare centers contacted)

### **Secondary endpoints regarding acceptance of seroprevalence testing**

- Acceptance of (finger-prick) blood sampling stratified by children and childcare workers (proportion of all scheduled finger-prick blood samples performed successfully)

### **Exploratory analyses of potential predictors of acceptance**

- Association between initial consent / drop out regarding respiratory sample collection and:
  - age/ sex of child
  - family/household size
  - employment status, educational level
  - assigned screening module
  - personal assessment of the dangers of a SARS-CoV-2 infection
  - personal opinions on the necessity of social restrictions in response to SARS-CoV-2 infections
  - personal experience of SARS-CoV-2 (e.g. cases of disease or death in family or among friends and acquaintances)
  - personal opinions on child vaccinations

### **Exploratory Analyses regarding psychosocial effects: Data collection using survey questionnaires related in terms of content to the coronavirus contact tracing app ("Corona-Warn-App") published by the Robert Koch Institute and additional qualitative interviews at the beginning and end of the intervention**

- Parents' satisfaction with the screening measure (weeks 1, 6, 12)
- Parents' sense of security due to the screening measure (weeks 1, 6, 12)
- Children's satisfaction (increase/decrease of anxiety, crying, defensive movements, refusal to attend daycare centre) (weeks 1, 6, 12)
- Subjective stress level caused by screening measure (weeks 1, 6, 12)
- Negative effects of screening measure on family climate (weeks 1, 6, 12)
- Organisation of daily routines affected by screening measure (weeks 1, 6, 12)
- Occurrence of effects personally perceived as negative consequences of the screening measures (e.g. quarantine period following a positive SARS-CoV-2 test) (weeks 1, 6, 12)
- Mental health symptoms according to validated questionnaires (weeks 1, 6, 12)

### **Qualitative Interviews: in-depth exploration of study participants' expectations and opinions before and after implementation of the intervention**

- Before the intervention: Participants' expectations, wishes and reservations regarding the measures to be introduced
- After the intervention: Personal experience of the measures, reasons for acceptance or lack of acceptance, potential barriers and obstacles to implementation

### **Children interviews after implementation of the intervention to determine acceptance (children questionnaire)**

- Children's acceptance (according to 3 questions); interview and documentation directly after sample collection (after 2, 6 and 12 weeks)

#### **Exploratory Analyses regarding effectiveness of the intervention**

- Proportion of all mid-turbinate swabs tested positive for SARS-CoV-2 (PCR)
- Proportion of all saliva samples tested positive for SARS-CoV-2 (PCR)
- Proportion of parents/siblings/others among all persons tested for SARS-CoV-2 (PCR) [Module 4]
- Proportion of absent days due to respiratory symptoms
- Proportion of absent days due to SARS-CoV2 infection of child and/or SARS-Cov-2 infection of a family member/other contact person (quarantine)
- Closures of daycare groups / daycare centers by the health authorities due to positive SARS-CoV-2 results within the research study
- Closures of daycare groups / daycare centers by the health authorities due to other causes
- Proportion of children and childcare workers with positive serological test result (antibodies) before and after the observation period of 12 weeks

#### **Exploratory Analyses regarding cost expenditure incurred by the intervention**

- Average costs per sample collection and index child, per week
- Average daily staff time required for study purposes per week (daily documentation of time estimated by physicians, helpers, childcare workers, parents (weeks 1, 6, 12))
- Average costs per detected case of SARS-CoV-2 infection (number and costs of tests carried out for the detection of one SARS-Cov-2 infection)
- Average number of absent days of children with potential COVID-19 symptoms (respiratory/ gastrointestinal symptoms)

An additional evaluation of acceptance will be carried out at the end of the study period based on the results of qualitative, semi-structured interviews in a subsample of participants.

#### **Exploratory Analyses regarding the proportion of other viral causes of respiratory symptoms**

- Detectable proportion of other respiratory viruses (e.g. rhinovirus, adenovirus, etc.) in respiratory secretions of children attending daycare centers during the SARS-CoV-2 pandemic

## **7.2 Data analysis methods**

The primary endpoints will be estimated as 95% confidence intervals using the Wilson score method. Due to the purely exploratory nature of all analyses and the fact that the four modules will be implemented in separate daycare centers, the significance level will not be adjusted for multiple testing and all analysis results will be interpreted with the necessary caution. The significance level will be set to 5% for all analyses. In a first step, descriptive analyses

(frequency (percent), mean (SD) or median (IQR)) will be reported for all endpoints. The analysis of the secondary endpoints drop out rate, initial rate of consent, acceptance of blood sampling (stratified by childcare workers and parents), proportion of positive serological tests and proportion of positive PCR tests will, in a first step, compare all four groups using test procedures such as the Chi-squared-test, ANOVA or the Kruskal Wallis test as appropriate. Subsequently, pairwise comparisons will be carried out using appropriate post-hoc tests. The rate of acceptance will first be compared between all modules 1 to 3 using the chi-squared test. Analysis of the development of the psychosocial factors over time will be stratified by monitoring module and will use tests for repeated measurements such as the McNemar test, Repeated Measurements ANOVA and the Friedman test. In addition, baseline values and the follow-up values after 12 weeks will be compared between modules using appropriate tests such as the chi-squared test and ANOVA or non-parametric tests followed by post-hoc tests. Potential predictors of the rate of acceptance will be analysed (overall for all modules combined and stratified by module) in univariable analyses using the chi-squared test and, if a sufficient sample size is obtained, additionally using multivariable logistic regression. The analysis of costs, the proportion of absent days and data on the closure of daycare groups will be restricted to descriptive methods. The development of seroprevalence data over time will be reported using descriptive methods, possibly including graphical displays. The results of the children interviews will be reported descriptively using frequencies. If possible, an ICC value (intraclass correlation) for the daycare centers will be calculated as a basis for sample size estimation for a future cluster randomised study. All analyses will be performed in SAS, R or SPSS.

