### 4.2 Informed Consent Process

After the consent of the daycare centre's management and sponsoring institution to implementation of the study has been obtained, all children's families and all childcare workers will receive information material and informed consent forms pertaining to the intended study and the specific module to be carried out in their daycare centre. The documents will be distributed by e-mail by the daycare centre's management. Parents/guardians and childcare workers will be asked for their consent to study participation separately for the following parts of the study: (i) initial questionnaire (paper questionnaire) (ii) further questionnaires (including pseudonymised electronic questionnaires, children interviews), (iii) respiratory sample collection, (iv) blood sampling, (v) guided interviews in a sample of participants. The number of parents/guardians and childcare workers declining participation in any part of the study from the outset will be recorded; if possible, they will be asked to state the reasons for their complete denial of consent. For respiratory sample collection and blood sampling, the consent of both parents/guardians will be required, for the other study parts (questionnaires and interviews) the consent of one parent/guardian will be sufficient. Parents/guardians will be asked to print the informed consent forms and hand in the completed forms in a sealed envelope at the daycare centre. If required, printed versions of the informed consent forms can be provided at the daycare centre. Sealable envelopes pre-addressed to the central study office will also be deposited at the daycare centre for the parents/guardians.

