#### 4.3.2 Psychosocial Dimension (questionnaire)

Successful implementation of the intended monitoring measures is highly dependent upon the acceptance by parents, children and daycare centers. As yet, no systematic data is available on the extent of willingness to participate in such preventive measures in the SARS-CoV-2 pandemic or on the acceptability of such measures. Analysis of the feasibility of the four monitoring protocols must therefore be accompanied by both quantitative and qualitative research elements involving all persons concerned. The feasibility study will furthermore offer the opportunity to gather data on factors potentially affecting acceptance of the monitoring measures in order to identify potential targets for accompanying interventions aimed at increasing the level of acceptance.

The Wü-KiTa-CoV study will gather questionnaire-based data on the acceptance of the respective monitoring protocol by parents/guardians, children and childcare workers three times during the study period (at the beginning of the study period and during and after the implementation of the measures). Families with more than one participating child will be asked to fill in separate questionnaires per child. The following potential predictors of acceptance will be examined:

- a) sociodemographic factors (e.g. educational level, place of residence, number and ages of children)
  - b) Expectations and opinions of the parent/guardian regarding the measures to be introduced
  - c) Existence and severity of mental health symptoms (anxiety and depression in particular).
- The assessment of mental health symptoms will be based on questionnaires using validated psychometric instruments/scores (e.g. PHQ4, EQ-5D and a short form of CBCL) and a sociodemographic question battery which is also used within the CORONA HEALTH APP Study in cooperation with the Robert-Koch Institute (PI: [name], Co-PI: [name]).

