### **7.5 Sample size discussion and power analysis**

Due to the study design as a feasibility study, the primary endpoint for modules 1-3 is the rate of acceptance of the respective surveillance protocol, defined as the proportion of children and childcare workers with successful participation in sample collection (mid-turbinate swab or saliva sample) among all children and childcare workers in the daycare centre. Parent/child groups and childcare workers who do not consent to participation in the study will be included in the calculations as “non-successful” participants. Each study participant will be classed as “successful” with respect to sampling if at least 60% of all scheduled samples were collected successfully. All persons with a positive serological test for SARS-CoV-2 will be classed as “successful” with regard to the primary endpoint as no further sample collection (mid-turbinate swabs or saliva samples) is to be carried out in these cases according to the surveillance protocol.

As the maximum achievable sample size will depend on the number of children and number of childcare workers per centre, it is only possible to state a minimum sample size per module. The estimates of precision will be based on this minimum sample size. If the sample size is greater than expected, the width of the precision estimate will be reduced, allowing a more precise estimation.

The inclusion criteria result in the following minimum sample sizes (number of children and childcare workers) per module:

Module 1 (intensive monitoring / mid-turbinate swabs): 105

Module 2 (extensive monitoring / mid-turbinate swabs): 105

Module 3 (intensive monitoring / saliva samples): 185

Module 4: 275

We assume that the rate of acceptance will depend on the frequency of sampling and the type of sample collection. Based on this assumption, we expect a lower rate of acceptance in module 1 (mid-turbinate swabs twice a week) than in module 2 or 3. We therefore assume the following rates of acceptance:

Module 1 (intensive monitoring / mid-turbinate swabs): 30%

Module 2 (extensive monitoring / mid-turbinate swabs): 37.5%

Module 3 (intensive monitoring / saliva samples): 37.5%

Reasoning for sample size in module 1 (intensive monitoring / mid-turbinate swabs):

A minimum number of 100 children and 5 childcare workers is sufficient to estimate a rate of acceptance of 30% with a precision (half the width of the 95%-CI using the Wilson score method) of max. 9.1%.

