Reasoning for sample size in module 2 (extensive monitoring / mid-turbinate swabs):

A minimum number of 100 children and 5 childcare workers is sufficient to estimate a rate of acceptance of 37.5% with a precision (half the width of the 95%-CI using Wilson score method) of max. 8.7%.

Reasoning for sample size in module 3 (intensive monitoring / saliva samples):

A minimum number of 175 children and 10 childcare workers is sufficient to estimate a rate of acceptance of 37.5% with a precision (half the width of the 95%-CI using the Wilson score method) of max. 6.9%.

Module 4:

The primary endpoint for module 4 is the proportion of cases with successful sample collection (i.e. completion of sample collection and diagnostic analysis – or receipt of test result in the case of external testing – within 72h after first telephone contact with hotline) among all cases relevant for sample collection. Testing will be carried out for all symptomatic parents, symptomatic children or childcare workers and further symptomatic household members after obtaining informed consent. The potential number of tests recommended will depend on the number of children and childcare workers in the module, the household size per family and the

proportion with acute respiratory illness (ARI). The (ARI)-physician consultation incidence in Germany varies between 400 and 2,500 per 100,000 inhabitants per week . We assume that the proportion with ARI in our study will correspond to the ARI physician consultation incidence at times of high prevalence as we reckon with a large number of unrecorded cases and the research study will be carried out during a period of high prevalence. We furthermore assume that module 4 will include 250 parent/child groups plus 25 childcare workers. According to data of the German Federal Statistical Office for 2018, the average family size is 3.5 persons . Based on this data, the following expected number of recommended tests is derived:

number of recommended tests = household size \* (children+childcare workers) \* proportion with acute respiratory illness per week \* observation period in weeks

$$=3.5*275*0.025*12= 279$$

We assume that 70% of all sample collections planned will be successful. A number of 279 recommended tests will be sufficient to estimate a 70% proportion of successful sample collections with a precision (half the width of the 95%-CI using the Wilson score method) of 5.4%.

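### The Modules 1–3 primary Wilson intervals and the precisions in 7.5 treat siblings as independent persons, so the nominal 95% intervals are somewhat too narrow

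*Protocol*

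**What the plan says.** - **Method (Protocol 7.2).** "The primary endpoints will be estimated as 95% confidence intervals using the Wilson score method", and "The significance level will be set to 5% for all analyses". No family-level term appears. The only clustering quantity mentioned is a daycare-centre intraclass correlation, to be computed if possible, for planning a later trial.
- **Unit (7.5).** The Modules 1–3 endpoint is "defined as the proportion of children and childcare workers with successful participation in sample collection" among everyone in the centre. Non-consenters count as unsuccessful.
- **Counts (7.5).** "Module 1 (intensive monitoring / mid-turbinate swabs): 105"; "Module 2 (extensive monitoring / mid-turbinate swabs): 105"; Module 3: 185.
- **Stated precision (7.5), as half-width of the Wilson interval.** Module 1 at most 9.1 points at 30%, Module 2 at most 8.7 at 37.5%, Module 3 at most 6.9 at 37.5%. For Module 3: "A minimum number of 175 children and 10 childcare workers is sufficient to estimate a rate of acceptance of 37.5" per cent.
- **Families.** Section 4.1 aims to enrol all children of a centre, and 3.2 admits ages 1 to 8. Section 4.3.2 says "Families with more than one participating child will be asked to fill in separate questionnaires per child".
- **Who decides.** Section 4.2: "For respiratory sample collection and blood sampling, the consent of both parents/guardians will be required". Under 4.3.1.6, parents in Module 3 take every saliva sample after the first one at home.

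The protocol does not state what share of children have a sibling in the same module or how strongly siblings' outcomes agree.

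**The concern.** A Wilson interval on n persons is a binomial calculation and assumes n independent outcomes. When parents refuse sampling, all their children in the centre are likely to become failures together. At the assumed acceptance of 30–37.5%, most persons are failures, and refusal is one direct route to failure. In Module 3, siblings also share the adult who does the sampling.

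Positive correlation within families makes the variance of the acceptance rate larger than binomial. The 95% interval then covers less often than stated, and the precision that justifies the sample size is optimistic. The same holds for individual-level chi-squared tests of family-level predictors such as household size, education and opinions (7.1, 7.2).

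These are the primary intervals of three of the four modules. They describe how certain one can be about acceptance when choosing protocols for the later cluster-randomised study (1.6).

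**Working it through.** **1. The plan's own figures under independence**

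Half-width = z·√[p(1−p)/n + z²/(4n²)] / (1 + z²/n), with z = 1.96 and z² = 3.8416. Inputs n and p are from 7.5.

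- Module 1 (n = 105, p = 0.30): 1.96·√(0.002000 + 0.0000871)/1.0366 = 0.0864, i.e. 8.64 points. Stated: 9.1.
- Module 2 (n = 105, p = 0.375): 1.96·√(0.002232 + 0.0000871)/1.0366 = 0.0911, i.e. 9.11 points. Stated: 8.7.
- Module 3 (n = 185, p = 0.375): 1.96·√(0.001267 + 0.0000281)/1.0208 = 0.0691, i.e. 6.91 points. Stated: 6.9.

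Module 3 reproduces, so no design effect was applied. The Module 1 and 2 figures do not reproduce where they stand, but they fit each other's place. With whole-number counts, 32/105 gives 8.68 and 39/105 gives 9.09. No variant tried gives both figures as printed: Wald gives 8.77 and 9.26, and continuity-corrected Wilson gives 9.10 and 9.56.

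**2. Design effect from sibling pairs**

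Let s be the share of children with one sibling in the module and ρ the within-pair correlation of success. Childcare workers are not paired. Then DEFF = 1 + (children/n)·s·ρ and effective n = n/DEFF. Both s and ρ are assumptions.

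- Low corner (s = 10%, ρ = 0.5), Modules 1 and 2: 1 + (100/105)·0.05 = 1.048. Module 3: 1 + (175/185)·0.05 = 1.047.
- High corner (s = 40%, ρ = 1): 1 + (100/105)·0.40 = 1.381, and 1 + (175/185)·0.40 = 1.378.

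| Module | Stated | Independent | s=10%, ρ=0.5 | s=20%, ρ=0.8 | s=40%, ρ=1 |
|---|---|---|---|---|---|
| 1 | 9.1 | 8.64 | 8.84 | 9.25 | 10.10 |
| 2 | 8.7 | 9.11 | 9.31 | 9.75 | 10.63 |
| 3 | 6.9 | 6.91 | 7.07 | 7.40 | 8.08 |

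The half-width grows by about 0.2 to 1.5 points.

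**3. When each stated precision is lost**

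- Module 1: above DEFF of about 1.11. It still holds at s = 10%, ρ = 1 and at s = 20%, ρ = 0.5 (9.03 in both).
- Module 2: already lost at DEFF = 1.
- Module 3: above DEFF of about 1.01, after rounding.

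**4. Coverage of the plain Wilson interval**

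Simulation with 200,000 runs per scenario gave, for Modules 1, 2 and 3:

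- No siblings: 94.6%, 95.7%, 95.1%
- s = 20%, ρ = 0.8: 92.7%, 94.1%, 93.5%
- s = 40%, ρ = 1: 89.7%, 91.3%, 90.8%

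The low corner was not simulated. The normal approximation 2Φ(1.96/√DEFF) − 1 gives 2Φ(1.915) − 1 = 94.4% at DEFF 1.048 and 2Φ(1.668) − 1 = 90.5% at 1.381.

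**5. Family-level predictors**

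If siblings share both predictor and outcome dependence to this degree, the size of a nominal 5% test is the complement of these values, about 5.6% to 9.5%.

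**The case against.** - **Siblings are not copies of each other.** Success needs at least 60% of that child's own scheduled samples (7.1), and children's refusals are recorded apart from parental withdrawal and by age. In Modules 1 and 2, trained staff swab at the centre, and parental swabbing is only a possible later option (4.3.1.6). Module 3 excludes children under 2, which removes some pairs. Section 4.2 does not say that one decision covers all siblings. This stands: near-identity of siblings is not supported. It lowers ρ but does not make it zero.
- **The size is assumed.** This also stands. The direction follows from any positive correlation; the amount depends on two quantities the protocol does not give.
- **A reader might infer that siblings cause all three stated precisions to fail.** The protocol does not support that. Module 1 has slack because its printed figure is too large, and Module 2 misses its figure even with independent children. Only Module 3 fits that reading.
- **A reader might infer that a module could be wrongly classed as successful.** Section 7.1 compares the acceptance rate with 30% or 37.5% and does not use the interval, and the precondition for the later study (1.6) refers to the same criteria. Interval width changes no classification.
- **All analyses are labelled exploratory (7.2).** That wording justifies omitting a multiplicity adjustment and urges caution. It does not turn an interval with 90–94% coverage into a 95% interval. For the predictor tests it carries more weight. Moreover, the initial questionnaire refers to an index child (4.2), so several rows per family are not established there.
- **The statistical analysis plan may handle it.** It is not at hand, but the protocol itself fixes the method in 7.2 and the figures in 7.5.

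**Conclusion.** The point holds as a moderate one. The Modules 1–3 primary intervals and precisions ignore correlation between siblings, although the protocol foresees siblings and a shared parental decision.

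Over the assumed range of s and ρ, the half-widths become 8.8–10.1, 9.3–10.6 and 7.1–8.1 points, with coverage of roughly 90–94%. What is overstated is the certainty reported around the acceptance rate. The rate itself and the success classification are unaffected.

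Module 3's 6.9 is lost with almost any sibling correlation, and Module 1's 9.1 only above a design effect of about 1.11. Module 2's 8.7 is wrong for a different reason: the Module 1 and 2 figures appear exchanged. The exchange is inferred from the arithmetic; the protocol does not say so. The predictor tests are a secondary, exploratory matter.

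**What to change.** 1. **Data.** Put a family code on the participant lists. For non-consenters, obtain from the centre roster only anonymous counts of sibling sets.
2. **7.2.** For Modules 1–3, compute the primary interval as a Wilson interval on the effective sample size (n divided by the estimated sibling design effect), or by a family-level bootstrap.
3. **7.5.** Correct the independent-case precisions to 8.6 (Module 1) and 9.1 (Module 2), and keep 6.9 (Module 3). Add the range under a stated sibling design effect, for example the one in the table. Merely noting that the printed figures hold without siblings would leave the Module 2 figure wrong.
4. **Predictor tests.** Cluster by family only where a family code exists. Section 4.2 has non-participants' initial questionnaires completely anonymised. For them, an anonymous family code would have to be set on the form before anonymisation; roster counts cannot supply that link.

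**Cost.** A small data-handling step, which needs planning before consent forms go out, and slightly wider stated precision. No extra participants.
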